
### Sample size calculation

The primary outcome of the study is the change in the proportion of patients with one or more (confirmed) diagnoses covering the symptomatic spectrum. For the sample size calculation we assumed that the innovative care will increase the percentage of patients receiving one or more confirmed diagnosis during the evaluation process from 30% with standard care to 40%. When planning the ZSE-DUO project, no applicable published information was available on the success rate of standard care in German CRDs. Thus, the assumed 30%-rate of patients with confirmed diagnoses using standard care was based on the experience and a consensus among the leading physicians of the eleven CRDs participating in this project. An absolute increase in patients with confirmed diagnosis of 10% by innovative care was considered realistic and clinically relevant by the group so that 40% overall success rate were assumed for this care model.

Power calculations were done using Monte-Carlo simulation. Data sets were generated assuming randomly varying center specific baseline prevalence rates (with an average of 95% of rates falling between 20 and 40%) and odds-ratios (with an average of 10% of centers not experiencing any positive intervention effect). For each simulated data set, center-specific odds ratios were calculated and then summarized using random-effects meta-analysis..

Based on enrollment varying between 24 and 93 patients per center and period and assuming a drop-out rate of 20%, the inclusion of 682 participants per group resulted in an estimated statistical power of 80.8% within 100,000 simulations, with a mean prevalence across simulations of 30.3% in the SC group and of 40.3% in the IC group. Statistical power was estimated as the percentage of simulations in which the random effects meta-analytic summary estimate of center-specific odds ratios was statistically significant at the 5% level.

### Data processing and statistical analysis

Data collection and analysis are coordinated and performed by the Institute for Clinical Epidemiology and Biometry at the University of Würzburg, the Institute for Epidemiology, Social Medicine and Health Systems Research at Hannover Medical School, and the Department of Medical Psychology in Hamburg.

For the primary outcome “Proportion of patients with one or more (confirmed) diagnoses covering the full symptomatic spectrum”, a mixed logistic regression model including a fixed period effect along with random center effects and random period effects nested within centers will be employed. In a second step, models will be extended by adding personal characteristics of patients (e.g., sex and age) and interaction terms between these characteristics and period. Significant interactions would suggest modification of intervention effects by the respective characteristics. While statistical significance of main effects will be defined at the 5%-level, it will be defined at the 10% level for interactions.

Secondary analyses are carried out in an exploratory way and results will be reported with 95%-confidence intervals. According to the distribution of the variables, differences between groups are tested using the χ2 test, Fishers’ exact tests, Student's t test, Mann–Whitney *U* test as well as univariable and multivariable linear regression models and mixed regression models. The incremental cost effectiveness ratio as a measure of efficacy is calculated by dividing the additional costs by the additional outcomes (QALYs) of IC versus SC. The non-parametric approach of bootstrapping is applied to estimate 95% confidence intervals of the incremental cost effectiveness ratio. The predictive value of applied standardized screening instruments will be analyzed for identifying patients affected by mental disorders. First, via exploratory factor analysis, it will be tested if the number of items of the applied screening instruments can be reduced. The new set of items will then be tested in a confirmatory factor analysis to examine how well this model fits the current data. Based on a reduced screening instrument a new score for mental disorders will be estimated using multivariable logistic models and the predictive value will be analyzed applying Receiver Operating Characteristic Graph (ROC-Graph). Qualitative interviews will be transcribed and data will be analyzed using MAXQDA.

All statistical analyses will be performed using SPSS, STATA and SAS, respectively.

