## Methods

### Study design

ZSE-DUO is a multi-center, prospective, controlled trial with a two-phase cohort design (Clinicaltrials.govIdentifier: NCT03563677). Eleven CRDs in Germany recruit individuals with a suspected rare disease but unclear diagnosis. Study participants of the control group are consecutively enrolled during the first 12 months of the project and are diagnosed and treated according to the Standard Care (SC) procedures. Participants of the intervention group recruited during the following 16 months receive the Innovative Care (IC) procedures which integrate the dual expert components (see Fig. 1). For recruitment of the IC group, the period had to be extended from 12 months—as originally planned—to 16 months because of stops in recruitment during the COVID-19 pandemic. Due to the nature of the patients, settings and interventions a sequential cohort design with the IC group following the SC group was preferred over a randomized trial, as blinding of participants and team members is not possible and cross-contamination between groups might have occurred in a randomized design.

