### Randomization

No randomization will be conducted since allocation to control and intervention conditions will occur based on timing of recruitment. However, participants will not be informed about allocation when informed consent is obtained. Thus, participants consent to all innovative care components even if they will receive standard care only.

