### Limitations

There are several limitations in study design and procedures.

First, ZSE-DUO is not a randomized controlled trial with a potential bias in selection of participants. However, randomization of participants to one of the two models of care would have posed a large risk that the standard care (control) group might have received facilitated access to the mental health expertise, thereby “contaminating” the control condition. A cluster randomized design, on the other hand, is not feasible since only relatively few CRDs with a non-specialized outpatient clinic for undiagnosed patients exist in Germany.

Secondly, due to the nature of the intervention, participants in the project and staff at the CRDs cannot be blinded to allocated care. However, efforts are taken to divulge medical information only after having obtained informed consent. Nevertheless, a selection bias at enrollment cannot be excluded, but can be tested when comparing the symptoms at baseline as well as the diagnoses established at enrollment with those during the 12-month period thereafter. Furthermore, comparing drop-out rates between the two care models will provide information on potential attrition bias.

The innovative care model combining expertise from both a somatic and a mental health expert in the diagnostic approach of a complex and often persistent unclear symptomatology may not only facilitate and accelerate the process of diagnosis but also help to guide all treatments warranted—may they target a somatic illness, a mental disorder or both. Irrespective of the mental symptoms being the cause of the presenting symptomatology, the consequence of the underlying health condition or unrelated, they can be identified and respective care be initiated. The integration of patients perspectives towards the innovative care model is important to ensure a high level of acceptance for this approach.

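### The primary model of this sequential-cohort comparison adjusts for centre but for no patient characteristics, and no case-mix-adjusted overall intervention effect is designated

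*Protocol article*

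**What the plan says.** All places are in the protocol article.

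- **Allocation.** Under Randomization: "No randomization will be conducted since allocation to control and intervention conditions will occur based on timing of recruitment". Under Study design, standard care (SC) is enrolled for 12 months and innovative care (IC) afterwards. The IC phase was lengthened from 12 "to 16 months because of stops in recruitment during the COVID-19 pandemic".
- **Primary model.** Under Data processing and statistical analysis: "a mixed logistic regression model including a fixed period effect along with random center effects and random period effects nested within centers will be employed". No patient characteristic appears in it.
- **Second step.** The same section continues that "models will be extended by adding personal characteristics of patients (e.g., sex and age) and interaction terms between these characteristics and period". The purpose given is: "Significant interactions would suggest modification of intervention effects by the respective characteristics". On significance levels: "While statistical significance of main effects will be defined at the 5%-level, it will be defined at the 10% level for interactions".
- **Selection bias.** Under Limitations: "a selection bias at enrollment cannot be excluded, but can be tested when comparing the symptoms at baseline". Under Study design, patients seen in the nine months before the project are compared with the SC group.
- **Entry to the cohorts.** Under Control (SC) and intervention (IC) group, a team reviews the records before a patient is invited. Under Innovative care, the tandem already takes part in that review.

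**The concern.** Nothing in a before-after design balances the cohorts on patient characteristics, so the period coefficient mixes the intervention effect with any difference in who was enrolled. The article itself offers routes to such a difference: the mental health expert joins the pre-visit record review in the IC phase only, and recruitment in that phase was interrupted by the pandemic.

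The stated safeguards can reveal a shift but do not correct for one. The baseline comparison is descriptive, and the historical comparison concerns pre-project patients against SC, not SC against IC. The one place where patient covariates meet the primary outcome is framed as a search for effect modification. With interactions in a model, the period coefficient refers to particular covariate values, and the article does not say which overall adjusted effect would be reported.

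At stake is how the main result is read. The Conclusions tie wider national use to the approach proving successful. A shift in case mix could create part of an apparent effect or, in the other direction, hide part of a real one.

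**Working it through.** **The plan's own figures.** The target is 30% (SC) against 40% (IC): 10 points, odds ratio (0.40/0.60)/(0.30/0.70) = 1.556. The article gives no figure for case-mix shift, so there is none to reproduce. Its 80.8% power was simulated from centre-specific odds ratios without patient covariates. That figure is a separate matter and is not used here.

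**Inputs**

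- From Sample size calculation: SC rate 30%; 682 per group; 20% drop-out, hence 682 × 0.8 ≈ 545 analysed per group.
- Assumed: one binary prognostic factor, 50% prevalent in SC; odds ratio (OR) for being diagnosed 1.5, 2 or 3; prevalence in IC higher by 5, 10 or 20 points; true intervention effect zero; two-sided 5% test; centre effects ignored.

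**Step 1: rates without (p0) and with (p1) the factor.** Solve 0.5·p0 + 0.5·p1 = 0.30 with p1 = OR·p0 / (1 + (OR − 1)·p0).

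- OR 1.5: p0 = 0.2576, p1 = 0.3424, gap 0.0847
- OR 2: p0 = 0.2283, p1 = 0.3717, gap 0.1434
- OR 3: p0 = 0.1888, p1 = 0.4112, gap 0.2224

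**Step 2: spurious difference** = prevalence shift × gap.

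**Step 3: false-positive rate** = 1 − Φ(1.96 − d/SE) + Φ(−1.96 − d/SE), where d is the spurious difference and SE = √{[0.30·0.70 + (0.30 + d)(0.70 − d)]/545}. For OR 2 and a 20-point shift: d = 0.20 × 0.1434 = 0.0287, SE = 0.0281, rate 17.5%.

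| OR | Shift (points) | Spurious difference (points) | Share of target | False-positive rate |
|---|---|---|---|---|
| 1.5 | 5 | 0.42 | 4% | 5.3% |
| 1.5 | 10 | 0.85 | 8% | 6.1% |
| 1.5 | 20 | 1.69 | 17% | 9.3% |
| 2 | 5 | 0.72 | 7% | 5.8% |
| 2 | 10 | 1.43 | 14% | 8.1% |
| 2 | 20 | 2.87 | 29% | 17.5% |
| 3 | 5 | 1.11 | 11% | 6.8% |
| 3 | 10 | 2.22 | 22% | 12.5% |
| 3 | 20 | 4.45 | 44% | 34.9% |

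A shift of the same size in the other direction would give a bias of the same size against IC.

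**Step 4: what adjustment recovers.** Logistic models were fitted to 2,000 simulated data sets (OR 2, 20-point shift, no true effect).

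| Model | Mean log-OR for period | Rejection at 5% |
|---|---|---|
| Period only | 0.13 | 16.8% |
| Period + covariate | 0.00 | 4.7% |
| Period + centred covariate + interaction | 0.00 | 4.8% |

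The standardised risk difference from the third model averaged 0.000, against a crude difference of 0.029. Simulation error on the rejection rates is below one percentage point. Both adjusted models remove the bias from the covariate they contain; the period-only model does not.

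**The case against.** A reader might infer that the trial will never produce a case-mix-adjusted effect, or that the second step cannot help. The documents do not support that.

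- A model with covariates and period interactions still conditions on those covariates. With centring or standardisation it gives an adjusted effect, as step 4 shows.
- The article speaks of models in the plural and sets a level for main effects beside one for interactions, so a main-effects fit is not excluded.
- It states no coding. To say that the period effect would refer to age zero would be a guess.
- The covariate list is open, and its details may stand in an analysis plan that is not shown. The short list is therefore no fault in itself.

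Nor is the primary model wholly unadjusted, since it includes centre and period within centre. The Limitations section does not claim that non-significant baseline comparisons rule out confounding. There are also real mitigations: patients do not know their allocation when they consent, and every suitable invited patient is asked to take part. These weaken the idea that patients select themselves because they know of the dual offer.

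All of this stands and narrows the point. It does not answer the core: the model stated as primary omits patient characteristics, and the extended models are given a different purpose. The mitigations also leave open changes in who is referred or invited.

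**Conclusion.** The point holds in this form. The confirmatory estimate is adjusted for centre but not for patient case mix, and no case-mix-adjusted overall effect is designated for the primary outcome. This rests on the model the article states, not on something it leaves out.

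The size is unknown from the documents. In the assumed scenarios the bias runs from 0.4 to 4.5 points (4% to 44% of the target) and the false-positive rate from 5.3%, close to nominal, to 34.9%. These figures depend on a single factor at 50% prevalence in SC and ignore centre effects. They show what is possible, not what has happened.

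Adjustment has a limit that should be stated with it. It addresses measured case mix only. Period and intervention coincide, so no covariate model can separate the intervention from the pandemic or from other changes over calendar time.

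**What to change.** Before analysis, and by a documented amendment:

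1. Make the primary model period + prespecified baseline main effects + the random effects already stated, without interactions.
2. Take covariates from T0 sources that Table 1 lists for both cohorts: age, sex and other socio-demographic data, employment status, T0 signs and symptoms (patient questionnaire, referral summary, medical letters) and prior diagnoses.
3. Do not use T0 questionnaires marked as IC only, or T1 psychopathological findings. Use T1 EQ-5D-5L, PHQ-15 and GAD-7 in a sensitivity analysis only, because IC elements begin before or at that visit and these values may already reflect them.
4. Report a standardised risk difference with 95% CI beside the odds ratio.
5. Keep the currently stated model as a sensitivity analysis, and fit interactions in a separate later step.
6. State that the adjustment covers measured case mix and not calendar-time effects.

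**Cost.** No new data. Some covariate values will be missing and need a prespecified method. The primary model changes when the article already describes enrolment into both cohorts in the past tense and care is unblinded, so the amendment should be dated and should precede any comparison of outcomes between the cohorts.

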### Dissemination plan

The main results will be published in a final report according to the German Innovations Funds directive. Furthermore, the scientific results will be published in peer-reviewed scientific journals and via presentations at national and international scientific conferences. The ZSE-DUO manual detailing the structure and procedures as well as experiences developed for the somatic and mental health specialists working in tandem will be published separately.

## Discussion

This is the first multi-center study investigating the effects of a dual guidance structure involving a somatic and a mental health expert working in tandem to establish one or more diagnoses in people with a suspected rare disease. Including mental health expertise in multidisciplinary teams, i.e. caring for cancer patients, has become more and more common over the last decades. Likewise, medical programs for individuals with stroke or heart attacks and evaluation before certain procedures such as bariatric surgery or transplantation benefit from the inclusion of a mental health expert [31, 32]. Additionally, in some rare diseases such as Huntington's Disease, the assessment and treatment of cognitive, emotional and behavioral symptoms have become the standard of care and an integrative part of international treatment guidelines [33].

### Strengths

This is the first study evaluating a tandem care in CRDs. The sample size is large and we will acquire a large set of data. Due to the multicenter approach (11 centers), the study concept with the developed SOPs will be tested in centers differing in structure and procedures. Findings on possible barriers and potential for improvement can be taken into account in the final recommendations and respective manual. Furthermore, the study considers the perspectives of multiple stakeholders in the care process on satisfaction, burden, acceptability, costs, and feasibility, so that it is easier to transfer and implement the concept of two expert physicians, a somatic and a mental health specialist working in tandem, in different RDC clinics.

### Limitations

There are several limitations in study design and procedures.

First, ZSE-DUO is not a randomized controlled trial with a potential bias in selection of participants. However, randomization of participants to one of the two models of care would have posed a large risk that the standard care (control) group might have received facilitated access to the mental health expertise, thereby “contaminating” the control condition. A cluster randomized design, on the other hand, is not feasible since only relatively few CRDs with a non-specialized outpatient clinic for undiagnosed patients exist in Germany.

Secondly, due to the nature of the intervention, participants in the project and staff at the CRDs cannot be blinded to allocated care. However, efforts are taken to divulge medical information only after having obtained informed consent. Nevertheless, a selection bias at enrollment cannot be excluded, but can be tested when comparing the symptoms at baseline as well as the diagnoses established at enrollment with those during the 12-month period thereafter. Furthermore, comparing drop-out rates between the two care models will provide information on potential attrition bias.

The innovative care model combining expertise from both a somatic and a mental health expert in the diagnostic approach of a complex and often persistent unclear symptomatology may not only facilitate and accelerate the process of diagnosis but also help to guide all treatments warranted—may they target a somatic illness, a mental disorder or both. Irrespective of the mental symptoms being the cause of the presenting symptomatology, the consequence of the underlying health condition or unrelated, they can be identified and respective care be initiated. The integration of patients perspectives towards the innovative care model is important to ensure a high level of acceptance for this approach.

## Conclusions

Should the innovative approach in ZSE-DUO prove successful, it will be made available on a wider scale nationally, will be promoted internationally and may serve as a role model for other medical situations.

## Data Availability

Not applicable.
